## Abstract

**Background:**

The frequent occurrence and increasing severity of major emerging infectious diseases (MEIDs) have posed considerable public health, economic and social issues worldwide. The emergency preparedness of public is inadequate to respond to and recover from MEIDs. Due to the limitation of time, space and resources, it is also difficult to carry out large-scale emergency preparedness training related to MEIDs. Then we developed a virtual interactive training system to improve emergency preparedness of public, including preparation of legal compliance, emergency knowledge, emergency capacity, economic estimation, material reserve and physical and mental health.

**Methods:**

A protocol for conducting a randomized controlled trail to evaluate the People’s War against Pandemic, a virtual interactive training system aimed to improve emergency preparedness of public for MEIDs. During the intervention, participants need to complete the storyline task at least once a day, watch at least one article and one video in the knowledge corner, and complete a retest of wrong choices in the intelligent evaluation module. The primary outcome is emergency preparedness of public for MEIDs. The secondary outcome is prevention and control knowledge of MEIDs.

**Discussion:**

The People’s War Against Pandemic may be an effective approach to provide public with a panoramic understanding of the response to MEIDs, so as to promote their comprehensive preparation and finally achieve effective response.

**Trial registration:**

This study was funded in 2021 and registered in the Chinese Clinical Trial Registry (registration number: ChiCTR2200060919) in June 2022. Recruitment and enrollment of participants began in July 2022.

## Background

In the past two decades, major emerging infectious diseases (MEIDs) including SARS, H7N9 avian influenza, Ebola fever, Middle East respiratory syndrome and Corona virus disease 2019 (COVID-19) have had considerable disastrous impact worldwide [1]. Particularly, COVID-19 has had an unprecedented impact on human lives and health, social stability and economic development [2]. Meanwhile, a series of global changes has increased the risk from MEIDs, making pandemics like COVID-19 likely to occur more frequently [3]. Public is the first responder to emergencies and is most likely to achieve self-rescue and mutual-rescue before and after emergencies [4]. To respond to and recover from the pandemics, it is necessary for public to make emergency preparedness.

In 2007, Nelson et al. [5] defined public health emergency preparedness as “the capability of the public health and health care systems, communities, and individuals to prevent, protect against, quickly respond to, and recover from health emergencies, particularly those whose scale, timing, or unpredictability threatens to overwhelm routine capabilities.” The object of emergency preparedness is not only the government and institutions, but also individuals at the public level. However, research on emergency preparedness of public in various countries shows that the public is usually underprepared [6–8], mainly reflected in lack of preparedness in emergency knowledge and skills. Due to the limitation of time, space and resources, it is also difficult to carry out large-scale emergency preparedness training related to MEIDs [9].

With the rapid development of mobile Internet and information technology, emergency education based on Internet plays an important role in public emergency response [10]. Among them, virtual interactive emergency training can break through the limitations of time, space and resources to provide the public with large-scale, homogeneous, low-cost and safe emergency preparedness training. In response to MEIDs, preventive medicine, nursing and emergency management department actively carry out virtual interactive training research [11, 12]. The training content of those studies is limited to the training objectives of professionals and lacks the real needs of emergency preparedness of public. In view of this, we constructed a training content framework for emergency preparedness of public for MEIDs including 20 knowledge, emotion and behavior tendency covering five aspects (cooperating with prevention and control work, improving emergency response ability, guaranteeing supplies and equipment, preparing economic resources, and maintaining physical and mental health), and developed a virtual interactive training system to improve emergency preparedness of public [13].

Below we describe a protocol of our randomized controlled trail to evaluate the effect of the virtual interactive training system intervention to improve emergency preparedness of public. The intervention, called The People’s War against Pandemic, is a 2-week virtual interactive training, designed to improve the ability of public to prevent, respond to and recover from MEIDs, including preparation of legal compliance, emergency knowledge, emergency capacity, economic estimation, material reserve and physical and mental health.

## Methods

### Study design

The design type of this study is a randomized controlled trial. Study participants will be recruited from public volunteers and allocated to one of the three randomized groups after completing a baseline survey (Fig. 1) (The People’s War Against Pandemic intervention group 1, The People’s War Against Pandemic intervention group 2, Control group). Three follow-up visit assessments are required to complete for participants at four weeks later, three months and six months after the intervention. Our hypotheses are:There is no statistical difference between The People’s War Against Pandemic intervention group 1 and The People’s War Against Pandemic intervention group 2 in prevention and control knowledge of MEIDs and emergency preparedness of MEIDs.Comparing The People’s War Against Pandemic intervention group 1 and Control group, the former group will have better effect on improve prevention and control knowledge of MEIDs and emergency preparedness of MEIDs.Comparing The People’s War Against Pandemic intervention group 2 and Control group, the former group will have better effect on improve prevention and control knowledge of MEIDs and emergency preparedness of MEIDs.

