
### Intervention design: overview

#### The People’s War Against Pandemic intervention group 1

Participants are asked to use The People’s War Against Pandemic for a two-week intervention. Participants need to complete the storyline task at least once a day, watch at least one article and one video in the knowledge corner, and complete a retest of wrong choices in the intelligent evaluation module. Researchers check the completion of participants through the user management module, and those who fail to complete will be reminded by sending text messages or phone. The effect of the intervention will be evaluated by using the same questionnaire as applied in the baseline survey at week one and two of intervention. Before the training, participants will be informed that they will be rewarded with 50 RMB after completing daily tasks and questionnaire.

#### The People’s War Against Pandemic intervention group 2

Participants are asked to use The People’s War Against Pandemic for a four-week intervention. Other requirements are the same as those of intervention group 1. The effect of the intervention will be evaluated at week 1, 2, 3, 4 of intervention. The purpose of setting this group is to explore the optimal duration of the training, so that the participants will neither fail to achieve the training effect due to too short time nor get bored due to too long time.

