### Data management and statistical analysis

Data will be collected, recorded and managed by the Survey Star, an online questionnaire platform (www.wjx.cn, Changsha Ranxing Information Technology Co., Ltd in China) to ensures the safety, integrity and consistency of the data. Researchers will download the data from Survey Star and save it in text format to a password-protected server. SPSS 21.0 analysis software was used for data analysis by the third party who did not participate in the intervention.

Data will be collected at baseline and descriptive statistics will be used to show the characteristics of each arm at baseline. The outcome indicator prevention and control knowledge of MEIDs is a binary variable, so the chi-square test will be used to compare among the three arms at the intervention completion, 1, 3, and 6 months after the intervention. Analysis of Variance (ANOVA) will be used to find out whether there are differences among the three arms in the outcome indicator-emergency preparedness of public for MEIDs. Repeated Measures ANOVA will be used to measure weather there are differences in emergency preparedness of public for MEIDs score at 1, 3, and 6 months after intervention. A Bonferroni correction will be used for multiple testing. Intention-to-treat analysis will be used to account for the influence of attrition. The difference was statistically significant when *P* ≤ 0. 05.

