Three arms were designed in this research, including two intervention arms and one control arms. Participants in the two intervention groups will receive The People’s War Against Pandemic to complete the storyline task at least once a day, read at least one article and watch one video in the knowledge corner, and complete a retest of wrong choices in the intelligent evaluation module. The difference between the two groups is the intervention time. Due to the interactivity of virtual interactive training system, participants may have different outcomes in different training. To explore the optimal duration to finish all the outcomes, we designed two-week and four-week groups, so that the participants will neither fail to achieve the training effect due to too short time nor get bored due to too long time. By comparing the intervention groups with the control group, it can be found whether The People’s War Against Pandemic is better than autonomous learning in improving emergency preparedness of MEIDs for public. By comparing the two intervention groups, we can find out the optimal duration to improve emergency preparedness of MEIDs for public.

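### Hypothesis 1 predicts no statistical difference between the 2-week and 4-week groups, but only tests of difference are planned, so a non-significant result would count as support without showing that the durations are equivalent

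*Protocol article*

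**What the plan says.** Study design lists three hypotheses. The first is that "There is no statistical difference between The People’s War Against Pandemic intervention group 1 and" intervention group 2 in knowledge and preparedness. The other two compare each intervention group with control and are directional: "the former group will have better effect on improve prevention and control knowledge of MEIDs and emergency preparedness of MEIDs".

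The two intervention groups differ in duration, two weeks against four. Of the 4-week group, Intervention design says: "The purpose of setting this group is to explore the optimal duration of the training". The Discussion goes further: "By comparing the two intervention groups, we can find out the optimal duration to improve emergency preparedness of MEIDs for public".

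Data management and statistical analysis plans the following:
- for preparedness, "Analysis of Variance (ANOVA) will be used to find out whether there are differences among the three arms", plus a repeated measures ANOVA over the follow-up visits;
- for knowledge, "the chi-square test will be used to compare among the three arms" at completion and at each follow-up;
- for multiplicity, "A Bonferroni correction will be used for multiple testing", with significance declared at P ≤ 0.05.

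The Recruitment section sizes the trial with a two-sided formula for a difference between two means, with α = 0.05, power 0.8, SD 26.31 and T = 3 comparisons. It arrives at 171 per group, raised to 206 for 20% attrition. No section gives an equivalence or non-inferiority margin, or a rule based on a confidence interval.

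**The concern.** Hypothesis 1 is phrased as a result to be expected, and the planned tests can only reject that result or fail to reject it. A failure to reject is compatible with equal durations, but also with a difference that the trial was too imprecise to see. Nothing in the plan separates the two cases.

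As worded, the hypothesis also becomes easier to support as information is lost: fewer completers, a larger SD or a stricter multiplicity threshold each raise the chance of a non-significant result. The article's own Limitations section expects loss of participants during follow-up.

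At stake is the reason for having the 4-week arm. If the predicted result occurs, a recommendation that two weeks suffice could rest on a test that failed to find a difference. A significant result would be informative, but only about which of these two durations scores higher.

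**Working it through.** **Inputs.** From the Recruitment section: SD 26.31, α = 0.05, power 0.8, T = 3, 171 per group before attrition, 206 after, attrition 20%. Three arms give three pairs, so T = 3 includes group 1 against group 2, and the per-comparison two-sided level is 0.05/3 = 0.0167 (z = 2.394). The analysis section names no separate test for this pair; a pairwise comparison at that level is inferred from T = 3 and the Bonferroni statement.

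**The plan's own figure.** The formula is n = 2[σ(z₁₋α/(2T) + z₁₋β)/(μA − μB)]². The text gives no value for μA − μB, so 171 cannot be reproduced independently. Solving backwards: 26.31 × √(2/171) × (2.394 + 0.842) = 9.21 points. Putting 9.206 back into the formula returns 171. The 9.2 used below is therefore an inferred figure.

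**Precision of group 1 minus group 2.** Completers per arm after the planned loss: 206 × 0.8 = 164.8. SE = 26.31 × √(2/164.8) = 2.898. The 95% half-width is 1.96 × 2.898 = 5.7 points.

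**Chance of a non-significant result.** For true difference d, P = Φ(2.394 − d/2.898) − Φ(−2.394 − d/2.898).

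| True difference (points) | In SD units (d/26.31) | P(non-significant) |
|---|---|---|
| 0 | 0 | 98% |
| 3 | 0.11 | 91% |
| 5 | 0.19 | 75% |
| 7 | 0.27 | 49% |
| 9.2 | 0.35 | 22% |

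Without the Bonferroni adjustment (two-sided 0.05, 165 per arm) the figures are 59% at 5 points and 11% at 9.2. With only 100 completers per arm (an illustration, SE 3.72) and the 0.05/3 level, they rise to 85% and 47%, which shows how attrition favours hypothesis 1.

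**What the present size could support if sameness were tested properly.** The article gives no margin M, so a range is assumed, with a true difference of 0, one-sided 0.025 and 164.8 per arm. Equivalence power (95% interval inside ±M) = 2Φ(M/2.898 − 1.96) − 1, set to 0 if negative. Non-inferiority power = Φ(M/2.898 − 1.96).

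| Assumed margin (points) | Equivalence power | Non-inferiority power |
|---|---|---|
| 5 | 0% | 41% |
| 7 | 35% | 68% |
| 8 | 58% | 79% |
| 9.2 | 78% | 89% |

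At a margin of 5, the expected half-width of 5.7 already exceeds the margin. For 80% power at that margin, equivalence would need 582 completers per group and non-inferiority 435. A margin of 9.2 would treat as equivalent a difference as large as the one the trial appears sized to detect.

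**The case against.** Several points can be made for the plan.

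*Hypothesis 1 may be only a formal null.* This fits poorly, because it stands in one list with two directional predictions. Even on that reading, nothing planned would allow sameness to be concluded.

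*The article never says that a non-significant P will be taken as equivalence.* This stands. A reader might infer a fixed rule that turns P > 0.05 into equivalence and then into a choice of duration. The documents do not state one: the analysis section defines only when a difference is significant, and the Discussion does not say how a null result will be interpreted. The point is therefore a risk created by the wording. It remains real because a hypothesis of no statistical difference, met only by tests of difference, offers no other criterion for support.

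*The duration question is exploratory.* The description of the 4-week group uses exploratory language, and so does part of the Discussion. This softens the claim, but the no-difference statement is still listed as the first hypothesis, and the Discussion also says the optimum can be found.

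*A separate analysis plan may set a margin.* It may, and the absence of one in an article is not the fault raised here. The fault is the stated hypothesis and the stated inference, which a later margin would have to replace.

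A reader might also take ANOVA to be the only test involved. It is not: hypothesis 1 covers knowledge too, for which chi-square tests are planned, and repeated measures ANOVA is added for preparedness.

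**Conclusion.** The point holds as a mismatch between hypothesis 1 and the planned methods. The result that the article predicts could be supported only by a failed test of difference, and that test would fail about three times in four at a true difference of 5 points and about half the time at 7. These figures rest on the article's SD, normal approximations, 164.8 completers per arm and a pairwise comparison at 0.05/3. They apply to preparedness only; no equivalent calculation is possible for knowledge, because the article gives no planning figures for it.

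Two stronger conclusions are not supported. The trial as a whole is not undermined: the comparisons with control in hypotheses 2 and 3, the randomisation and the data collection are untouched. Nor does it follow that a switch to an equivalence or non-inferiority design comes free at the present size; that depends wholly on the margin. The point should be fixed before analysis, but it concerns how one comparison is interpreted.

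**What to change.** 1. Restate hypothesis 1 as estimation: the trial will estimate the difference between the 2-week and 4-week groups in preparedness and in knowledge.
2. Report group 1 minus group 2 with its 95% confidence interval for both outcomes. For preparedness the expected half-width is about 5.7 points. For knowledge the interval should be on the scale finally used, since the article describes a 17-item score in one section and a binary variable in another (a separate matter).
3. State that a non-significant comparison will not be read as no difference.
4. In the Discussion, replace the claim that the optimal duration can be found with a statement that the difference between two and four weeks will be estimated.
5. Claim equivalence, or non-inferiority of two weeks to four, only if the sponsor justifies a margin before unblinding, separately for each outcome, decides from the confidence interval, and states the power that the present size gives at that margin.

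Steps 1 to 4 cost only wording and need no further participants; the price is a weaker statement about duration. Step 5 may not be achievable with 206 per group unless the margin is wide: under the assumptions above, non-inferiority has 79% power at 8 points and equivalence 78% at 9.2.

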**Fig. 1 Fig1:**
[figure not shown]
Study flowchart

### Study participants

This study aims at improving the emergency preparedness of public for MEIDs. Public is the target population of this study. Inclusion criteria are 1) public aged 16-60; 2) Participants have clear consciousness, no mental disorders, and have access to the Internet and be able to use computers or smart phones; and 3) Participants sign informed consent and voluntarily participate in the study. Exclusion criteria include any of the following 1) Ongoing or already on emergency preparedness for MEIDs intervention; and 2) Unable to cooperate to complete the evaluation of relevant outcome indicators. Dropout criteria include any of the following 1) Participants lose contact and voluntarily withdrew from the study; and 2) Participants are unable to complete the study due to illness or accident.

### The People’s War Against Pandemic: overview

Under the guidance of multi-disciplinary theoretical framework (interactive narrative theory [14], situated learning theory [15], human-computer interaction theory [16]), we completed the scheme design and system development of virtual interactive training system for emergency preparedness of public for MEIDs. Participants can enter the system through computers, mobile phones, and tablets, and can log in for free after registration. The interface of the system is shown in the Fig. 2.

**Fig. 2 Fig2:**
[figure not shown]
Interface of the system. (There are 6 interfaces in the picture. Interface 1 is the login interface; Interface 2 is the knowledge corner; Interface 3 is the map of different scenes; Interface 4 shows the scene of the high-speed railway carriage; Interface 5 is a warning interface for the virtual character infected with the disease after the training fails; Interface 6 shows the scene at home)

#### Training content

The training content index system was constructed based on the global national-level emergency preparedness index framework [17]. The training content index system includes five first-level indices (cooperating with prevention and control work, improving emergency response ability, guaranteeing supplies and equipment, preparing economic resources, and maintaining physical and mental health) and 20 s-level indices and their connotations including knowledge, emotion and behavioral tendency related to emergency preparedness for MEIDs.

#### Background storyline

The background storyline of the virtual interactive training system is the outbreak of a MEID in a certain place, and participants need to identify and analyze the harmfulness and controllability of the pandemic development according to the pandemic spread data. In each period of the pandemic spread, participants can act in each scene according to the storyline development and avoid infection with themselves and others through the correct selection in key interactive nodes. Participants can acquire knowledge and skills of prevention and control of MEIDs, adjust emergency emotion and change behavior tendency.

#### Module

Virtual interactive training module: This module is the core module of the system and the first module displayed after participants registration and login. Click start training to enter the background introduction interface, which introduces the purpose, requirements and steps of the training. Then enter the map interface, which is the display interface of each scene. Participants select the scene according to the prompt. Each scene has different tasks, which are set according to the training content index system. After the training task of one scene is completed, participants can choose to enter the next scene. During the training, each interactive interface will display the participants' current score (full score is 100), training time, current city, pandemic data and task bar. Participants make choices at interactive nodes based on the development and harmfulness of the pandemic. Every choice made at the interactive node is related to the success or failure of the training. The interactive interface of successful participants will prompt “you passed the training”, and those who have not passed will prompt “you failed”, and corresponding pictures will appear to show a series of disasters, including direct disasters (sick with the virus, pandemics spread globally) and indirect disasters (secondary disasters such as social, economic and cultural disasters), as a warning.Knowledge corner module: This module contains knowledge and skills of MEIDs (including source of infectious, route of transmission, susceptible population, clinical manifestation, prevention and control measures), laws and regulations on the prevention and control of public health emergency, secondary disasters.Intelligent evaluation module: This module records the behaviors and choices of participants in the training process and gives intelligent scores. Taking the training content indices as specific scoring points, the system judges each behavior and choice of the participants, scores the correct behavior or choice, and does not score the wrong one, and finally forms a training report. The training report shows a radar chart of training score, time, number of training sessions, and each behavior and choice. Wrong choices in the training process can be re-tested to achieve the purpose of consolidating knowledge.Forum community module: Participants can leave insights, gains and experiences, system bugs, opinions and suggestions in this module.User management module: This module integrates the task release, data collection and integration, account management and score management, which can provide real-time and objective data for the prevention and control of MEIDs.
